### Neuropsychological assessment

For cognitive screening, we will use the Mini-Mental State Examination (MMSE) and Montreal Cognitive Assessment (MoCA) [20, 21] MMSE is more sensitive for detection of dementia, whereas MoCA was specifically designed to capture milder forms of vascular cognitive impairment. All patients undergo an extensive and standardised neuropsychological assessment [22, 23]. This test battery covers global cognitive functioning and 4 major cognitive domains: memory, executive functioning, attention/psychomotor speed and language [24]. Tab. 3 presents an overview of the cognitive tests and domains.

**Table 3 Tab3:** Neuropsychological test battery^a^

Cognitive domain	Cognitive tests
Memory	15-Word-Auditory Verbal Learning Test: total immediate recall, delayed recall and recognition score Visual Association Test: part A
Language	Visual Association Test: naming
Attention and psychomotor speed	Trail Making Test: part A Stroop Colour Word Test: card I and II Letter Digit Substitution Test Digit Span: forward condition
Executive functioning	Trail Making Test: index score of part B/A Stroop Colour Word Test: interference score Digit Span: backward condition
Global cognition	Mean score of 4 domains
Global cognitive screening	Montreal Cognitive Assessment Mini-Mental State Examination Modified Telephone Interview for Cognitive Status [25]^b^ Telephone Montreal Cognitive Assessment [25]^b^
Depressive symptoms	Geriatric Depression Scale
Apathy symptoms	Starkstein Apathy Scale
EuroQol-5D including Visual Analog Scale	Health-related quality of life

^a^ For references to individual tests, see Table S2 in Electronic Supplementary Material

^b^ If neuropsychological assessment cannot be performed in person, Modified Modified Telephone Interview for Cognitive Status and Telephone Montreal Cognitive Assessment will be used, which can be conducted via telephone

Neuropsychological tests will be performed by trained clinical neuropsychologists blinded to previous cognitive scores and imaging findings. Time of day, location and test sequence will be kept similar during baseline and follow-up visits. At 3 months and 1 year after TAVI, the neuropsychological assessment will be repeated. If patients are unable or unwilling to visit the Amsterdam UMC during follow-up, a telephone neuropsychological assessment will be offered, including the Modified Telephone Interview for Cognitive Status and the Telephone MoCA [25]. All neuropsychological assessments include the Geriatric Depression Scale (depressive symptoms), Starkstein Apathy Scale (symptoms of apathy) and EuroQol-5D including Visual Analog Scale [22, 23].

Neuropsychological test scores are standardised into Z‑scores, which are constructed as: (test score − mean baseline score) / standard deviation of test score. Z‑scores from available tests of each cognitive domain are averaged to create 4 cognitive domain scores. Patients will serve as their own controls, and Z‑scores are based on baseline cognitive test scores for baseline and follow-up. Detailed information on the neuropsychological assessment and analyses are presented in Tables S1 and S2 in the Electronic Supplementary Material.

### Other study variables

Other outcomes and adverse events will be defined and reported according to the third Valve Academic Research Consortium and NeuroARC consensus guidelines [24, 26].

### Sample size

Based on our pilot data [11], we hypothesise a 10% increase in CBF after TAVI. With an 80% power and α of 0.05, the required sample size is 126. If a TAVI procedure is complicated by the need for permanent pacemaker implantation, subsequent MRI follow-up will be contra-indicated. In addition, some patients will not be able to take part in all follow-up measurements due to concomitant disease, institutionalisation or death. As we estimate 21% of the patients will not be able to undergo follow-up MRI, a total of 152 patients are needed.

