### Patient population

Aortic valve stenosis is defined according to the most recent European Society for Cardiology Guidelines [2]. All consecutive patients scheduled for TAVI at the Amsterdam University Medical Centres (Amsterdam UMC) in Amsterdam, the Netherlands will be screened for study inclusion and approached for study participation at the outpatient clinic. Tab. 1 shows the inclusion and exclusion criteria for the study.

**Table 1 Tab1:** Inclusion and exclusion criteria of the CAPITA study

*Inclusion criteria*	
1	Presence of severe symptomatic aortic valve stenosis and eligible for TAVI
2	Able and willing to give informed consent
3	Aged > 18 years
*Exclusion criteria*	
1	Presence of an MRI contra-indication
2	Known neurological disease, excluding cerebrovascular events without sequelae
3	Active malignant disease
4	Insufficient mastery of the Dutch language
5	Non-atherosclerotic vascular disease (e.g. vasculitis)
6	Dialysis treatment for renal failure
7	Planned surgery with general anaesthesia within 3 months after TAVI

*TAVI* transcatheter aortic valve implantation, *MRI* magnetic resonance imaging

The Amsterdam UMC is a tertiary referral hospital where approximately 350 TAVI procedures per year are performed. A multidisciplinary Heart Team decides whether a patient is eligible to undergo TAVI and selects the access route and valve type. Transfemoral access with local anaesthesia is the default approach. If transfemoral TAVI is not feasible, transaortic access is also performed. Patients will be treated with the balloon-expandable Sapien 3 or Sapien 3 Ultra (Edwards Lifesciences Inc., Irvine, CA, USA) or the self-expandable Navitor (Abbott, Abbott Park, IL, USA) or Evolut R (Medtronic Inc., Minneapolis, MA, USA) transcatheter heart valve devices.

Patients will serve as their own controls: baseline measurements in the presence of severe aortic valve stenosis are compared with post-TAVI follow-up measurement. A control group with comparable aortic valve stenosis seems to be unfeasible, as we believe it is not ethical to delay TAVI in patients with a clinical treatment indication. Time intervals for follow-up assessments are 4 weeks before or after the scheduled visit.

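### The enrolment target of 152 adds 21% to 126 instead of dividing by 0.79, so at the planned loss about 120 patients are evaluable and power is about 78%, not 80%

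*Protocol article*

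**What the plan says.** The only sample size justification is in the Sample size section of the protocol article. It concerns CBF, one of the two co-primary outcomes: "we hypothesise a 10% increase in CBF after TAVI". The requirement follows: "With an 80% power and α of 0.05, the required sample size is 126".

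The section then gives reasons why a follow-up scan may be missing: a permanent pacemaker after the procedure, other illness, institutionalisation or death. It concludes: "As we estimate 21% of the patients will not be able to undergo follow-up MRI, a total of 152 patients are needed".

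The design is a single group measured before and after TAVI (Patient population): "Patients will serve as their own controls: baseline measurements in the presence of severe aortic valve stenosis are compared with post-TAVI follow-up measurement". The Statistical analysis section tests the change in CBF with a paired t-test or the Wilcoxon signed-rank test. A patient without the 3-month MRI therefore contributes nothing to this comparison. No other section gives a different loss rate or total.

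**The concern.** The 21% is expressed as a share of the patients, and the listed reasons act on people already in the study. The number with a follow-up scan is therefore 79% of the number enrolled, and the enrolment target should be the evaluable number divided by 0.79. The printed total is too small for that and coincides with the evaluable number multiplied by 1.21, a familiar slip.

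What is at stake is the stated power for the CBF co-primary outcome. The total was set specifically to absorb the expected loss. If it does not, a reader who takes the section at face value will believe that the study keeps 80% power at 21% loss, when on the plan's own figures it does not.

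**Working it through.** **Inputs, all from the Sample size section**

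- Evaluable patients required: 126
- Power 80%, alpha 0.05. Sidedness is not stated; two-sided is assumed, and one-sided is shown as well.
- Expected share without follow-up MRI: 21%
- Stated total: 152

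**Step 1. Reproduce the stated total.** Evaluable number × (1 + loss) = 126 × 1.21 = 152.46. This rounds to the printed 152 (153 if rounded up).

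**Step 2. Total that meets the requirement.** Evaluable number / (1 − loss) = 126 / 0.79 = 159.49, so 160. The printed total is 160 − 152 = 8 short.

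**Step 3. What 152 delivers at the planned loss.** 152 × 0.79 = 120.08, so about 120 evaluable patients. That is 126 − 120 = 6 short, or 6/126 = 4.8%.

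**Step 4. Loss that 152 can absorb.** 1 − 126/152 = 26/152 = 17.1%.

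**Step 5. Power at 120.** The SD of the change in CBF is not needed, because the pair of 126 patients and 80% power fixes the standardised paired effect. In the two-sided normal approximation:

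- implied effect = (1.960 + 0.842) / √126 = 0.2496
- power at n = 120 = Φ(0.2496 × √120 − 1.960) = Φ(0.774) = 78.1%

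Other versions of the same calculation, each set to give 80% at n = 126:

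| Test | Implied effect | Power at n = 120 |
|---|---|---|
| Two-sided, normal | 0.2496 | 78.1% |
| Two-sided, paired t | 0.2515 | 78.0% |
| One-sided, normal | 0.2215 | 78.3% |
| One-sided, paired t | 0.2227 | 78.3% |

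If 126 was itself rounded up, and 125 is taken as giving exactly 80%, power at 120 is 78.4% (two-sided t) or 78.5% (one-sided t). All versions lie between 78.0% and 78.5%.

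**Step 6. Chance of reaching 126.** If each patient independently has a 79% chance of a follow-up scan, the binomial probability of at least 126 scans is about 14% with 152 enrolled and about 58% with 160.

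**The case against.** The strongest counter-argument is that the total may be right and the percentage wrong. If the investigators expected 26 losses, then 126 + 26 = 152, and 26/126 = 20.6%, which rounds to 21%. On that reading 152 does deliver 126, and the percentage was merely taken on the wrong base. This cannot be excluded from the text, but it goes against the wording, which applies the percentage to the patients who enter the study. It also leaves an error in print, because the loss among enrolled patients would then be 26/152 = 17.1%. One of the three figures must change on either reading.

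A second objection is that 21% is a forecast, so the shortfall is conditional. That is correct. The article reports neither the number enrolled nor the number of follow-up scans, and 120 is what the plan implies, not an observed count.

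Third, the 78% is derived backwards, without a stated SD or sidedness. It does rest on taking the stated 126 and 80% at face value in a paired test, but it barely moves across the versions tried.

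Fourth, the practical effect is small: about 2 points of power, recruitment closed, and no endpoint or test altered. This stands and sets the weight of the point. The telephone follow-up described under Neuropsychological assessment does not help here, since it cannot replace an MRI.

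**Conclusion.** The point holds. The figures 126, 21% and 152 cannot all be right. Read as written, the enrolment target should be 160; 152 gives about 120 evaluable patients and about 78% power instead of 126 and 80%. This assumes that the 21% applies to enrolled patients, that the loss occurs as forecast, and that 126 gives 80% power in a paired comparison at alpha 0.05. It concerns CBF alone, not the cognitive co-primary outcome.

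This is a definite arithmetic error in a stated sample size and power, with a small effect. It needs correcting but does not threaten the study.

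**What to change.** Restate the sentence in the Sample size section, for example: with 152 patients enrolled and 21% without follow-up MRI, about 120 are evaluable for CBF, giving about 78% power at the effect for which 126 would give 80%; 160 would have to be enrolled to retain 126, and 152 tolerates a loss of at most 17%.

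If the investigators in fact planned for 26 losses, keep 152 and 126 and replace 21% with 17%, saying that the share is of enrolled patients.

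The Current status and timeline section puts the last baseline visit in October 2022, so no further enrolment is proposed. The cost is one corrected sentence, repeated wherever else the figures appear, and, on the reading as written, a stated power about 2 points lower.

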### Statistical analysis

Clinical data will be entered at CastorEDC.com to create the final dataset. Continuous variables will be tested for normality distribution with visual inspection and the Shapiro-Wilk test. Accordingly, differences between baseline and 3‑month follow-up in CBF, as well as cognitive global and domain-specific Z‑scores, will be tested with the paired-samples *t*-test or Wilcoxon signed-rank test.

Change in global CBF (ml/100 g per min increase from baseline) will be assessed as a predictor of change in cognitive functioning (Z-score) using mixed models analysis adjusted for sex, age and education. Additionally, change in cardiac output (in l/min) will be assessed as a predictor of change in CBF with mixed models analysis. Other clinical parameters, including blood pressure, will be assessed as potential confounders of change in CBF and cognitive functioning. Finally, we will examine the association of 1‑year cognitive Z with CBF and cognitive functioning during prior visits.

### Ethical consideration

The study is conducted in accordance with the Declaration of Helsinki and the Dutch Medical Research Involving Human Subjects Act (*Wet medisch-wetenschappelijk onderzoek met mensen*). The study protocol was approved by the Medical Ethics Committee of the Amsterdam UMC. All patients must provide written informed consent before participating.

### Current status and timeline

The first patient was included in August 2020, and the last patient’s baseline visit was performed in October 2022. One-year follow-up visits are scheduled and ongoing.

## Discussion

The CAPITA study is the first study that will extensively assess cognitive and cerebral outcomes in patients with severe aortic valve stenosis undergoing TAVI. In this population, cognitive impairment is prevalent in 21–39% of patients [3, 4, 6, 8]. The pathophysiology of this impairment is most likely multifactorial: increased WMH prevalence at baseline, restricted cardiac output, and overlapping risk factors for cognitive impairment and aortic valve stenosis [1, 3, 11]. Treating aortic valve stenosis with TAVI may improve cardiac output [11] and potentially CBF.

CBF remains relatively constant within an autoregulatory range due to wall changes in cerebral vessels. Autoregulatory mechanisms of CBF are sensitive to changes in CO_2_ levels, mean arterial pressure and neurovascular signalling [27, 28]. Aortic valve stenosis may limit cardiac output to such an extent that it impairs CBF. Restoration of restricted cardiac output following TAVI may shift the autoregulatory curves to a new steady state, thereby increasing CBF [27]. In a pilot study, we found that every litre increase in cardiac output was associated with an 8.2% increase in global CBF [11].

Other studies showed that cognitive functioning is improved after TAVI in 11–19% of patients [4, 6–10]. Cognitive improvement was particularly seen in patients with pre-existing cognitive impairment and in those with smaller pre-interventional aortic valve areas [6–8]. In the general population, impaired CBF is associated with future cognitive decline and incident dementia [29]. If TAVI indeed improves CBF, it may protect against future cognitive decline. In patients with heart failure, the relation between reduced CBF and cognition has been more extensively studied. Here, heart failure treatment was associated with restored CBF and improved cognition, as observed after captopril initiation, cardiac resynchronisation therapy and heart transplantation [27]. Impaired CBF in heart failure patients correlates with disease severity and is predictive of clinical deterioration and death [30]. Hence, in patients with severe aortic valve stenosis, CBF may ultimately be used as an additional parameter for evaluation of disease severity.

The systematic approach of the current study also enables identification of potential risk factors for adverse cerebral and cognitive outcomes in patients undergoing TAVI. Pre-existing vascular risk factors for cognitive impairment and WMH prevalence may not improve after TAVI. Moreover, there is ample evidence of new brain lesions on MRI in the majority of patients undergoing TAVI [5, 9]. Therefore, the CAPITA study will also assess MRI measures of structural brain damage, i.e. microbleeds, infarcts and WMH at both baseline and 3 months after TAVI.

Personalised care and patient selection can be optimised if we can predict in which patients cognitive functioning improves after TAVI. Additionally, improvement of CBF and cognitive functioning following TAVI may suggest that cardiac interventions can benefit the brain.

### Study limitations

As the study was started during the COVID-19 pandemic, more attrition bias may be expected. However, we implemented telephone follow-up visits for patients who are unable to visit the hospital. In addition, baseline measurements can be impacted by distress due to the TAVI procedure, potentially affecting the neuropsychological assessment and outcomes. However, neuropsychologists are aware of the upcoming hospitalisation and practice empathy and compassion towards all patients, potentially minimising the confounding effects of stress.

## Conclusion

The CAPITA study is the first study to prospectively and systematically assess both positive and negative cerebral and cognitive outcomes in patients with symptomatic severe aortic valve stenosis undergoing TAVI. We hypothesise that TAVI improves cardiac output, CBF and cognitive functioning. The CAPITA study may facilitate risk stratification for adverse cerebral outcomes. CBF may ultimately be an indicator of severity of aortic valve stenosis. Furthermore, the study may render proof of concept that cardiac interventions can benefit the brain.
